# Efficacy of electroacupuncture in patients with failed back surgery syndrome: study protocol for a randomized controlled trial

**DOI:** 10.1186/s13063-021-05652-4

**Published:** 2021-10-14

**Keywords:** Failed back surgery syndrome, Electroacupuncture, Manual acupuncture, Sham acupuncture, Clinical trial

## Abstract

**Background:**

Persistent pain following back surgery called failed back surgery syndrome remains a major treatment challenge. The aim of this study is to evaluate the efficacy and safety of electroacupuncture on relieving back pain in FBSS patients.

**Methods/design:**

This is a randomized, single-blind, single-site, placebo-controlled trial. A total of 144 eligible FBSS patients will be randomly assigned to the electroacupuncture, manual acupuncture, or sham acupuncture group in a 1:1:1 ratio. Each group will receive 2 treatment sessions per week for 12 weeks. The primary outcome will be low back pain intensity based on the 11-point numerical rating scale (NRS). The secondary outcomes include Oswestry Disability Index (ODI) questionnaire, Beck Depression Inventory-II (BDI-II), Pittsburgh Sleep Quality Index (PSQI), and analgesic consumption. All clinical outcomes will be collected at baseline, during the treatment phase (at 8 and 12 weeks), and at the 16-, 24- and 36-week follow-ups. All data will be analyzed based on the intention-to-treat principle and adverse events will be assessed during the trial.

**Discussion:**

This pilot randomized controlled trial will evaluate the efficacy of electroacupuncture for treating failed back surgery syndrome. The outcomes will determine whether electroacupuncture is efficacious in relieving low back pain as well as improving the quality of life in failed back surgery syndrome patients.

**Trial registration:**

Chinese Clinical Trial Registry ChiCTR2000040144. Registered on 22 November 2020

**Supplementary Information:**

The online version contains supplementary material available at 10.1186/s13063-021-05652-4.

## Background

“Failed back surgery syndrome” (FBSS) is characterized by persistent or recurrent back and/or radiating leg pain, even after anatomically successful spinal surgery [1]. Despite the advances made in lumber surgical technologies, the incidence of FBSS is still reported in the range of 10 to 40% [2]. Chronic pain following FBSS can always interfere with physical, emotional, and social components of life, resulting in a considerable financial burden on the society [3].

Due to the complex etiologies and mixed neuropathic and nociceptive pain components, few management guidelines existed for FBSS [4–6]. In general, FBSS without structural deficit was usually managed with conservative treatments, including oral medication, nerve blocks, pulsed radiofrequency, and physiotherapy [7, 8]. FBSS cases with poor response to conservative treatments are often treated with spinal cord stimulation (SCS) [9]. However, SCS requires implantation of a permanent pulse generator and the implant materials are expensive, which is not suitable for all medical conditions and patients. Therefore, finding the optimal management of FBSS as a therapy that was effective, less complicated, and not invasive in nature has been always desired.

Acupuncture is a therapeutic intervention originated in China, which can treat diseases by the insertion of thin metallic needles through the skin at specific sites [10]. In recent years, acupuncture has been used as an integrative therapy for pain since well-tolerated with little risk of adverse effects [11]. Numerous systematic reviews have investigated that acupuncture has a therapeutic effect on chronic low back pain [12, 13]. And the mechanisms of acupuncture analgesic effect were reported to involve endogenous pain control systems, cerebral plasticity, and nonspecific effects [14].

Electroacupuncture (EA) is the application of electrical stimulation to acupuncture needles. Several studies demonstrated that EA exerted a quicker and stronger analgesic effect than manual acupuncture [15, 16]. Furthermore, evidence-based results also showed that EA was better than high-frequency transcutaneous electrical nerve stimulation (TENS) or sham acupuncture in the treatment of neuropathic pain [17]. However, the efficacy of EA or acupuncture for FBSS has not been reported specifically. Therefore, we designed this rigorous high-quality randomized controlled trial to provide valid evidence for the efficacy of EA in treating FBSS, compared with manual acupuncture and sham acupuncture treatment.

## Methods

### Study design and setting

This is a patient- and assessor-blind randomized, placebo-controlled clinical trial that will be conducted at Shanghai Municipal Hospital of Traditional Chinese Medicine. Eligible FBSS participants will be randomly assigned (1:1:1) to receive 24 sessions of electroacupuncture (EA), manual acupuncture (MA), or sham acupuncture (SA) over a 12-week treatment period and a 6-month follow-up period. The study will follow the recommendations of the Consolidated Standards of Reporting Trials (CONSORT) [18] and the protocol was reported in accordance with the Standard Protocol Items (SPIRIT) (Additional file 1). A flow chart of the study process is detailed in Fig. 1.

**Fig. 1 Fig1:**
[figure not shown]
Flow chart of study procedures

### Recruitment and ethics

The recruitment will be conducted at Shanghai Municipal Hospital of Traditional Chinese Medicine. Patients will be recruited throughout the patient clinic and hospital-based WeChat advertising. This study has been approved by the ethics committee of Shanghai Municipal Hospital of Traditional Chinese Medicine (No. 2020-SHL-KY-40), registered at the Chinese Clinical Trial Registry (ChiCTR2000040144), and will be carried out in accordance with the principles of the Declaration of Helsinki. All participants will be prioritized and asked to sign the informed consent before enrollment and have been given adequate time to consider what the trial involves. The study schedule of enrolment, intervention, and assessments is shown in Table 1.

**Table 1 Tab1:**
[figure not shown]
Schedule of enrollment, intervention, and assessments

### Inclusion criteria

Individuals will be recruited for the study if they satisfy the following criteria:

1. Aged 18–80 years

2. Primary diagnosis of FBSS [19] (in this study, FBSS is defined as low back and leg pain persist or recur for at least 6 months following at least one decompression and/or fusion procedure) and not requiring further surgery

3. Average low back pain score ≥6 on a 0–10 numerical rating scale (NRS)

4. On a stable dose of pain medications for at least 2 weeks prior to screening and willing to decrease the pain medication dose during the study

5. No evidence of failure to improve substantially with conservative management including but not limited to physical therapy, acupuncture, exercises, drug therapy, and bedrest

6. Willing to prohibit any treatment that may affect trial results other than acupuncture treatment

7. Competent to understand the study protocol and volunteer to write informed consent to participate

### Exclusion criteria

Individuals will be excluded if they have any of the following criteria:

1. Specific serious diseases that would be possible causes of spinal pain (e.g., malignant tumors, vertebral fractures, spinal infection, inflammatory spondylitis, cauda equina syndrome)

2. Consistent severe pain (10 out of 10 NRS) without fluctuation

3. Unsuitable for acupuncture or at risk of acupuncture-associated safety complications (e.g., hemorrhagic disease, patients under anticoagulant treatment, severe diabetes with risk of infection, serious cardiovascular or renal disease, skin lesions at the acupuncture site)

4. Medical conditions that would potentially influence the interpretation of treatment effect or results (e.g., diabetic neuropathy, epilepsy, dementia, psychiatric disease)

5. Pregnancy or planning pregnancy during the study period

6. Participation in another clinical study that would confound data

7. Unresolved issues of secondary gain (e.g., pending litigation)

### Randomization and allocation concealment

A randomization sequence will be computer generated by the statistician ([name]) who is not involved in the later statistical work of the study with SPSS 23.0 software, using block randomization with a block size of three or six. An independent researcher will prepare the sealed envelopes to ensure concealment of the allocation sequence. Eligible FBSS patients will be randomly assigned to the EA, MA, or SA group in a 1:1:1 ratio. Only the acupuncturist who performs the treatment will know the group allocation at the time of treatment.

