### Blinding

Although it is not practical to blind the acupuncturists to treatment allocations, all of the participants, outcome assessors, and statisticians will be subject to blinding. To achieve successful blinding, a pragmatic placebo needle will be employed and a sham acupuncture design will be applied, and all researchers will be trained before the trial begins.

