### Sample size

The trial was aimed to determine whether there was a difference among the EA group, MA group, and SA group in terms of NRS scores. The sample size was calculated based on the previous study [30] through the PASS system (version 15.0.5), with the assumption of the difference in the mean NRS scores between the MA group and SA group as 1.5 and the standard deviation as 2.0. Thirty-nine participants per group would be required to provide 90% power with a two-sided significance level of 5%. Therefore, considering a 20% dropout rate, a total of 144 participants will be recruited eventually in the study.

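### Published blocks of three or six, with unblinded acupuncturists, weaken concealment: for anyone who knows the running sequence, about 9% (equal masked mix) to 33% (all threes) of allocations are certain

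*Protocol article*

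**What the plan says.** All references are to the protocol article.

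- **Randomization and allocation concealment:** the sequence is computer generated by a statistician who takes no part in the later analysis, "using block randomization with a block size of three or six". The ratio is fixed: "Eligible FBSS patients will be randomly assigned to the EA, MA, or SA group in a 1:1:1 ratio". On concealment: "An independent researcher will prepare the sealed envelopes to ensure concealment of the allocation sequence". On knowledge of the arm: "Only the acupuncturist who performs the treatment will know the group allocation at the time of treatment".
- **Blinding:** "it is not practical to blind the acupuncturists to treatment allocations".
- **Abstract, Methods/design:** "This is a randomized, single-blind, single-site, placebo-controlled trial". No stratification is mentioned, so a single running sequence is assumed here.
- **Sample size:** "a total of 144 participants will be recruited eventually in the study".
- **Trial status:** recruitment was still under way when the article appeared.

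The article does not say whether the two sizes are mixed at random or one is used throughout, who opens the envelopes, or who enrols.

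**The concern.** With three arms at 1:1:1, three is the smallest block there can be: it holds one place per arm. Anyone who knows where a block of three begins and sees its first two allocations knows the third without opening an envelope. A sealed envelope hides the next arm only from a person who cannot deduce it.

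Printing the sizes during recruitment gave the set of possible sizes to anyone who read the article. Because treatment cannot be hidden from the acupuncturists, some people at the single site learn allocations as they are used.

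What is at stake is selection bias. If a person with influence on enrolment can guess the next arm better than chance, the timing or acceptance of a patient can depend on it. The primary outcome is a self-rated pain score, so differences between patients steered to different arms could reach it directly. The size of any such bias cannot be computed from the article.

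**Working it through.** The plan states no predictability figure, so there is none to reproduce. The inputs are block sizes 3 or 6, three arms at 1:1:1, one sequence (assumed) and N = 144. The observer is assumed to know all earlier allocations in order. An allocation counts as certain when every arm still possible for it is the same arm.

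**1. One fixed size, known**

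- *Block of 3.* Only the last place is certain: 1/3 = 33.3%, or 48 of 144. The best guess is right (1/3 + 1/2 + 1)/3 = 61.1% of the time.
- *Block of 6.* The last place is always certain. The fifth is certain too when the last two places belong to the same arm, which has probability 1/5. Expected certain places: 1 + 0.2 = 1.2. Share: 1.2/6 = 20%, or 0.20 × 144 ≈ 29. Enumerating all orderings gives a best guess of 56.1%.
- *For comparison.* Enumeration gives 1.286/9 = 14.3% for blocks of 9 and 1.333/12 = 11.1% for blocks of 12.

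**2. Threes and sixes mixed with equal chance, each block's size known**

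(0.5 × 1 + 0.5 × 1.2)/(0.5 × 3 + 0.5 × 6) = 1.1/4.5 = 24.4%, or about 35 of 144. If the share of threes is 25%, this becomes 1.15/5.25 = 21.9%. If it is 75%, it becomes 1.05/3.75 = 28.0%.

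**3. The same mix, sizes masked**

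The observer knows that sizes are 3 or 6 but not which applies. Two different arms at the start of the sequence then no longer settle the third place:

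- Two different arms occur with probability 1 in a block of 3 and 4/5 in a block of 6.
- The chance that the block is a three is therefore 0.5/(0.5 + 0.4) = 5/9.
- The remaining arm comes next with probability 5/9 + (4/9)(1/2) = 7/9, or 78%, not 100%.

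Over a whole sequence this was simulated with a Bayesian update after each allocation (3,000 sequences of 144). About 8.8% of allocations are certain (about 13 of 144; highest single run 18%), and the best guess is right about 57.7% of the time. With 25% to 75% of blocks being threes, certainty ranges from about 5% to 11%.

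**4. Larger masked mixes**

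Same method, equal chance of each size, 2,000 sequences per mix:

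| Sizes | Certain | Best guess correct |
|---|---|---|
| 3 / 6 (plan, if mixed and masked) | 8.8% | 57.7% |
| 6 / 9 | 5.1% | 54.1% |
| 6 / 12 | 5.7% | 52.7% |
| 9 / 12 | 3.9% | 51.7% |
| Chance alone | – | 33.3% |

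**The case against.** The strongest reply has three parts.

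First, a reader might infer that a third of this trial's allocations are predictable. The article does not support that. It names two sizes, and one third needs every block to be three. An equal masked mix gives about 9%. This part stands: one third is a ceiling, not what the plan fixes.

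Second, every percentage needs one observer with the full ordered sequence. The article gives knowledge of the arm only to the acupuncturist treating that patient, at the time of treatment. It speaks of acupuncturists in the plural, and each patient is treated in a separate space. With several acupuncturists, none need see the whole order. This also stands, so the figures are conditional.

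Third, a reader might infer that acupuncturists screen or enrol patients and so can act on a guess. Nothing in the article says so. Who enrols and who opens envelopes is operational detail that a condensed article commonly leaves to the full protocol, and silence about it is not a finding.

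It is also fair to say that permuted blocks of three or six are a recognised design, and that against a masked 3/6 mix the gain from larger blocks is modest. None of this removes what the article does state: the smallest possible block is allowed, and both sizes were made public during recruitment. Even the most favourable mix examined leaves a best guess well above chance.

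**Conclusion.** The point holds as a conditional weakness in a stated rule. For someone who knows the running order, certain predictions amount to 33% (all threes), 24% (equal mix, sizes known), 20% (all sixes) or about 9% (equal mix, sizes masked). The best guess is right between about 56% and 61% of the time across these designs, where computed, against 33% by chance.

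The figures assume a single unstratified sequence and an observer who has seen all earlier allocations in order; the mixed cases also assume an equal chance of each size. It does not follow that concealment is defeated: sealed envelopes prepared by an independent researcher still protect against anyone without that knowledge, and the article does not show that any such person decides on enrolment. This is a cheap improvement of optional priority.

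**What to change.** For the part of the sequence not yet used, drop block size three. Have the independent statistician generate larger, randomly mixed blocks, for example of 6, 9 and 12, and keep the sizes out of every document that treating or recruiting staff can see while recruitment lasts. Two-size masked mixes from this set give about 4–6% certain allocations and a best guess of about 52–54%. The three-size mix was not computed separately.

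The cost is a new set of envelopes for the remaining places and possibly a slightly uneven final split. If recruitment stopped inside a block of 12, two arms could differ by at most 4 participants, the number of places per arm in that block; for a block of 6 the limit is 2. Allocations already made are unaffected.

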### Blinding

Although it is not practical to blind the acupuncturists to treatment allocations, all of the participants, outcome assessors, and statisticians will be subject to blinding. To achieve successful blinding, a pragmatic placebo needle will be employed and a sham acupuncture design will be applied, and all researchers will be trained before the trial begins.

### Qualification of practitioners

Only licensed acupuncturists with at least 3 years of acupuncture experience will perform the treatment. All the acupuncturists will be instructed in standardized operating procedures prior to the start of the study, such as the location of acupoints and the depth of needling.

### Interventions

The interventions will be applied to eligible FBSS patients in three groups for 30 min for 24 sessions over 12 weeks (2 sessions per week). During the treatment, each patient will be placed in a separate quiet space and lying in the prone position, receiving one of the three treatments: electroacupuncture, manual acupuncture, or sham acupuncture. All the acupuncture procedures will follow the Standards for Reporting Interventions in Controlled Trials of Acupuncture (STRICTA) [20]. The location of acupoints for treating FBSS is shown in Fig. 2. In order to improve participants’ adherence, participants will accept the treatment for free and receive financial subsidies (200 RMB) after the last follow-up assessment.

**Fig. 2 Fig2:**
[figure not shown]
Location of acupoints for FBSS

#### The electroacupuncture group

Treatment will be performed using sterilized disposable steel needles (size, 0.35mm × 75mm; Wuxi Jiajian Medical Instrument Co., Ltd, Wuxi, China). Patients will receive acupuncture at bilateral acupuncture points Jiaji (EX-B2. L3, located 0.5cun [≈10mm] lateral to the lower border of the spinous process of the third lumbar vertebra), Jiaji (EX-B2. L4, located 0.5cun [≈10mm] lateral to the lower border of the spinous process of the fourth lumbar vertebra), and Jiaji (EXB2. L5, located 0.5cun [≈10mm] lateral to the lower border of the spinous process of the fifth lumbar vertebra). All acupoints were selected according to the literature [21, 22] and our clinical experience, located with reference to the WHO Standard Acupuncture Locations. After skin disinfection, needles will be inserted perpendicularly for all selected acupuncture points to a depth of 40 to 60mm. After achieving needling sensation [23], an electric stimulator (Huayi BT701-1B; Shanghai Huayi Medical Appliance Factory, Shanghai, China) will be connected to two pairs of needles (EX-B2. L3- EX-B2. L5 bilaterally) to deliver a continuous wave-type pulse at 20-Hz frequency current of 2mA. All needles will be retained for 30 min before removal.

#### The manual acupuncture group

Patients in the manual acupuncture group will undergo similar procedures as the electroacupuncture group except there will be no current output from the electrical apparatus. Sham electrical stimulation technique will be used with the needles connected to functioning electrical stimulators via broken wires.

#### The sham acupuncture group

In the sham acupuncture group, the sham acupuncture device Streitberger placebo needle will be used [24]. The acupoints, electrode placements, and other treatment settings are the same as for the sham electroacupuncture group but with no needling sensation.

### Scheme of analgesic use

The enrolled patients will be allowed to receive celecoxib capsules (Pfizer Pharmaceutica Co. Ltd., New York State, USA) orally on request with a maximum dose of 400 mg/day during the study treatments. The analgesia consumption will be recorded as research data.

### Permitted and prohibited concomitant treatments

During the treatment and follow-up period, participants will not be allowed to initiate any more pain control interventions, which includes but is not limited to other pain blocks, medications, surgeries, and physical therapy. However, general light exercises will be allowed. The researchers will advise the participants to avoid other treatments and re-emphasize at each evaluation time point. Once an individual has utilized other cointerventions, this information should be reported to investigators and recorded for analysis.

### Evaluation

Eligibility was assessed during an initial screening visit. Consent was obtained from all candidates, after which demographic data (age, gender, weight, height, body mass index), duration of pain in months, medical and surgical history, physical examination, segmental level of surgery, and radiographic investigations were taken.

### Outcomes

The primary outcome will be pain intensity of low back. The secondary outcomes will be functional disability, depression symptoms, sleep quality, and analgesic consumption. All outcome data were collected at baseline, during the treatment phase (at 8 and 12 weeks), and at the 16-, 24-, and 36-week follow-ups.

#### Primary outcome measurement

The primary outcome measure is the pain intensity of the low back assessed using an 11-point numerical rating scale (NRS) [9]. Patients will record their low back pain two times per day on a diary for 3 days prior to assessment. The pain intensity for each assessment was calculated as the average NRS available during that period.

#### Secondary outcome measurements

##### Functional disability

The Oswestry Disability Index (ODI) questionnaire will be used to assess functional disability due to FBSS. This questionnaire consists of 10-item scales with 6 response categories each. Each item scores from 0 to 5, which are transformed into a 0 to 100 scale, with scores 0 to 20 have a minimal disability, 21 to 40 have a moderate disability, 41 to 60 have a severe disability, 61 to 80 are crippled, and 81 to 100 are bed-bound or exaggerating their symptoms. A change in ODI of 6% is considered clinically meaningful [25].

##### Depression symptoms

The Beck Depression Inventory-II (BDI-II) is an instrument that assesses the severity of depression. It contains 21 items on a 4-point scale from 0 to 3 and the final score ranges between 0 and 63 points, which reflects the presence of depressiveness and severity thereof. The scores for depression are minimal (<14), mild (14–19), moderate (20–28), and severe (>28). Respondents are instructed to answer the items based on how they have been feeling over the past 2 weeks [26].

